**Translation of the approved study protocol (only methods section in agreement with editor)**

**Methods:**

*Design and recruiting:* The study is a randomized multicenter trial with 6 month follow-up with the participation of Regionalhospitals Silkeborg, Viborg, Horsens, Herning, and Aalborg University Hospital. A total of 140 patients with medically treated lung embolism (LE) will be included in the study, 70 in each group (Figure 1). The inclusion criteria are as follows: 1) objectively verified acute PE (ICD10 I260 and ICD10= I269); including recurrent LE; 2) treatment of LE with anticoagulant drugs; 3) 18–80 years of age; and 4) competency in the Danish language. Patients will be excluded in the case of: 1) PE as a secondary finding in relation to a scan performed due to another disease; 2) severe co-morbidity (e.g., severe heart disease, severe, active cancer, severe psychiatric disease, e.g. schizophrenia or depression). The nurses or physiotherapists at the cardiac wards of the participating hospitals will perform daily screening of patients hospitalized at the ward with the aim to recruit eligible patients according to the above criteria. On the day of discharge eligible patients are informed about the study, and the written study information is handed out (Appendix 1). Patients have a right to two days of deliberation time, and will be contacted by telephone hereafter to ask for participation in the project. By acceptance of participation written consent is retrieved (appendix 2) when the patients arrive for their baseline test in the AK-clinic (anti-coagulation clinic) app. 14 days after discharge. Following the baseline tests, patients are randomized to either the control group or the intervention group using opaque, sealed envelopes. Block randomization by hospital is used to ensure that approximately an equal number of patients at each hospital will be allocated to the control- and the intervention group, respectively.

[Figure 1. Flowchart as in manuscript]

**Outcomes and methods of measurement:** Data on patient's age, sex, BMI, medical treatment of LE, diagnosis (cause of LE) are retrieved from medical records at baseline.

- Primary outcome: Change in physical capacity, measured with the Incremental Shuttle Walk Test (appendix 3) from baseline to 6 months follow-up.
- Secondary outcomes: Change from baseline to 6 months follow-up on the following parameters:

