  - Disease-specific quality of life measured with the Pulmonary Embolism Quality of Life questionnaire
  - Generic quality of life measured with EuroQol-5 Dimensions
  - Sick leave (number of days in the past 4 weeks)
  - Use of painkillers and psychoactive drugs the past 4 weeks.

36  
37  
38  
39  
40  
41  
42  
43  
44  
45  
46  
47  
48  
49  
50  
51  
52  
53  
54  
55  
56  
57  
58  
59  
60  
61  
62  
63  
64  
65

The secondary outcome measures are collected in one questionnaire (appendix 4)  
The primary endpoint is 6 months after baseline test. In addition an intermediary measurement is performed 8 weeks after baseline (after termination of exercise program, see figure 1).

*The Incremental Shuttle Walk test (ISWT)* has been developed for assessing and measuring changes in a person's maximum walking capacity. The reliability and validity of the test has been shown in several studies and has been found acceptable. Studies show a reasonable association between maximal oxygen uptake and the ISWT, and that this association is better than the association between maximum oxygen uptake and the 6 minute walking test. The test has been validated within a number of study populations, including patients with heart and lung diseases [18].

The Pulmonary Embolism Quality-of-Life (PEmb-QoL) is a disease-specific quality of life questionnaire, containing six dimensions, covering frequency of complaints (8 items), activities of daily living (ADL) limitations (13 items), work-related problems (4 items), social limitations (1 item), intensity of complaints (2 items), and emotional complaints (10 items).

The EuroQol Five Dimensions (EQ-5D) is a generic quality of life questionnaire comprising both a descriptive part with 5 dimensions and the visual analogue scale EQ-VAS. The five dimensions mobility, self-care, usual activities, pain/discomfort, and anxiety/depression) [22, 23].

Sick leave and use of psychotropic drugs is gathered in questionnaires. Regarding sick leave the patient is asked to state the number of days' sick leave within the last four weeks according to the following categories: 0 work days; 1-4 days per week; 5-7 days per week. Regarding use of psychotropic drugs (e.g antidepressive medicine, anxiety reducing medication, sleeping pills) the patient is asked to state their average weekly use within the last four weeks according to the following categories: 0 days per week, 1-4 days per week, and 5-7 days per week.

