De sekundære effektmål er samlet i ét spørgeskema (Bilag 4).

Det primære endpoint er 6 måneder efter baseline måling. Herudover foretages også en intermediær måling 8 uger efter baseline (efter endt træningsforløb, se Figur 1).

*Incremental Shuttle Walk Test* (ISWT) er udviklet med henblik på at vurdere og måle ændringer i maksimal gangkapacitet [11]. Testens reliabilitet og validitet er belyst i flere studier og er generelt fundet acceptabel. Studier viser, at der er fornuftig sammenhæng mellem maximal iltoptagelse og ISWT, og denne sammenhæng er bedre end sammenhængen mellem maximal iltoptagelse og eksempelvis 6 minutters gangtest. Testen er valideret i en lang række sygdomspopulationer, herunder hos patienter med lunge- og hjerte/kar sygdomme [12].

*Pulmonary Emboli Quality-of-Life (PEmb-QoL)* er et sygdomsspecifikt livskvalitetsspørgeskema bestående af 9 overordnede dimensioner, der dækker emnerne *hyppighed af symptomer* (8 spørgsmål), *begrænsninger i dagligdags aktiviteter* (13 items), *arbejdsrelaterede spørgsmål* (4 items), *sociale begrænsninger* (1 item), *intensitet af symptomer* (2 items) og *emotionelle symptomer* (10 items)[13-15].

*EuroQol 5 Dimensions (EQ5D)* er et generisk livskvalitetsspørgeskema, bestående dels af en deskriptiv del med 5 dimensioner samt den visuelle analog skala EQ-VAS. De 5 dimensioner dækker over mobilitet, selvhjulpenhed, sædvanlige aktiviteter, smerter/ubehag og angst/depression [16, 17].

*Sygefravær og forbrug af psykofarmaka* indhentes ved brug af spørgeskema. For sygefravær bedes patienten angive deres samlede sygefravær indenfor de sidste 4 uger i følgende kategorier 0 dage; <5 arbejdsdage; <10 arbejdsdage; ≥10 arbejdsdage. For forbrug af psykofarmaka (fx antidepressiva, angstdæmpende medicin, sovemedicin) bedes patient angive deres ugentlige forbrug i de sidste 4 uger i kategorierne 0 dage, 1-4 dage per uge, 5-7 dage per uge.

Baselinemålingerne udføres af den fysioterapeut, der ser patienten i ambulatoriet, ca. 14 dage efter deres udskrivelse. De efterfølgende tests ved 8 uger og 6 måneder udføres af en projektfysioterapeut, der er blindet for, om patienten er i forsøgs- eller kontrolgruppen. Ved indkaldelse til opfølgende tests indskræpes det derfor overfor patienten, at de *ikke* må afsløre overfor den testende fysioterapeut, hvilken gruppe de har været i.

Tabel 1. Overblik over måletidspunkter:

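### The psychotropic-drug item has no answer category for use on 1 to 3 days in four weeks, so occasional users must be recorded either as non-users or as at-least-weekly users

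*Protocol*

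**What the plan says.** The secondary outcomes are introduced as "Secondary outcomes: Change from baseline to 6 months follow-up on the following parameters" and include "Use of painkillers and psychoactive drugs the past 4 weeks" (Protocol, English Methods, Outcomes and methods of measurement). For psychotropic drugs, the same section says that "the patient is asked to state their average weekly use within the last four weeks", and gives the categories "0 days per week, 1-4 days per week, and 5-7 days per week".

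The Danish text (Metode, Effektmål og målemetoder) has the same three categories: patients are to "angive deres ugentlige forbrug i de sidste 4 uger i kategorierne 0 dage, 1-4 dage per uge, 5-7 dage per uge". It asks for weekly use and has no word for average.

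Under Analysis and evaluation, the chi2 test is named for this outcome. Neither language version says where use on fewer than one day per week belongs. The questionnaire itself (appendix 4) is not among the documents shown.

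**The concern.** The recall period is four weeks but the categories are in whole days per week. They start at 0 and then jump to 1, so use that is real but less than weekly has no place. An occasional sleeping pill is an obvious example.

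The gap sits at the point that separates users from non-users. Two patients with identical use can be recorded differently, depending on how each one rounds. Because the outcome is change from baseline to 6 months, inconsistent rounding can create a change that did not happen: 2 days at both visits, ticked as 0 once and as 1-4 once. It can also hide one that did: no days at baseline, 2 days at 6 months, ticked as 0 both times. A chi2 test across the three categories and one on any use versus none are both affected, since both use the boundary between 0 and 1-4.

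**Working it through.** The protocol states no figure for this outcome, so there is none to reproduce. Its sample size of 60 per group is derived for the walk test only.

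**Coverage of the categories**

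Inputs: a recall period of 4 weeks, hence a total d of 0 to 28 days of use; categories 0, 1-4 and 5-7 days per week (English Methods). The average is d / 4 and moves in steps of 0.25.

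| Total days d | Average d / 4 | Category | Number of totals |
|---|---|---|---|
| 0 | 0 | 0 | 1 |
| 1, 2, 3 | 0.25, 0.50, 0.75 | none | 3 |
| 4 to 16 | 1 to 4 | 1-4 | 13 |
| 17, 18, 19 | 4.25, 4.50, 4.75 | none | 3 |
| 20 to 28 | 5 to 7 | 5-7 | 9 |

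Of the 29 possible totals, 1 + 13 + 9 = 23 are covered and 6 are not. Three of the six lie on the boundary between use and no use. The other three affect only 1-4 versus 5-7. This counts possible answers, not patients.

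Ticking 1-4 per week claims at least 4 days in four weeks. That overstates 3 days by a factor of at least 4/3, 2 days by at least 2, and 1 day by at least 4.

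**The Danish wording**

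Without averaging, the categories can be read as whole days in a usual week. The gap between 4 and 5 then disappears. The low end stays unresolved: one day of use in one of four weeks makes a usual week of 0, so a patient who did use the drug is recorded as a non-user. A patient who instead answers from the week with use ticks 1-4.

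**Illustration of what lost sensitivity could mean**

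The protocol gives no rates of use, so every rate here is an assumption. Take 60 patients per arm, any use compared between arms, two-sided 5%, and suppose that a share s of the users in each arm are occasional users who all tick 0. The recorded rates are p1(1 − s) and p2(1 − s), and with p̄ their mean:

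power = Φ{ [ |p1 − p2| − 1.96 √(2 p̄(1 − p̄)/n) ] / √( [p1(1 − p1) + p2(1 − p2)]/n ) }

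For 30% v 15% with s = 20%, the recorded rates are 24% v 12% and p̄ = 0.18. The numerator is 0.12 − 1.96 × 0.0701 = −0.0175, the denominator is 0.0693, and the power is Φ(−0.25) = 40%.

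| Assumed true rates | s = 0 | s = 20% | s = 40% | s = 60% |
|---|---|---|---|---|
| 20% v 10% | 33% | 27% | 21% | 15% |
| 30% v 15% | 50% | 40% | 30% | 21% |
| 40% v 20% | 67% | 54% | 40% | 27% |

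The assumption that every occasional user ticks 0 is extreme. If all of them ticked 1-4, the any-use comparison would lose nothing and only the amount of use would be overstated.

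**The case against.** The strongest objection is that the averaging arithmetic rests on the English text alone. The Danish text does not corroborate it, and the two versions differ elsewhere (upper age limit 80 in the English, 70 in the Danish), so neither can be used to settle the other. This stands for the 17-19 day gap, which should be claimed only under the English wording. It does not remove the low gap, because neither version has a category for less-than-weekly use.

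Second, the patient-facing questionnaire is not shown and might carry a rounding instruction. That is possible. The protocol text describes none, though, and the categories it does fix are incomplete as written.

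Third, this is an unpowered secondary outcome, and the number of missing totals does not measure harm. Both are true, and they limit the importance of the point.

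A reader might go further and infer that the item wrongly pools antidepressants, anxiety-reducing medicine and sleeping pills, so that a patient on one daily drug can never show change in another. The documents do not support raising this as an error. The classes appear only as examples in a parenthesis ("Regarding use of psychotropic drugs (e.g antidepressive medicine, anxiety reducing medication, sleeping pills"), the outcome is defined for psychotropic drugs as a group, and whether the questionnaire asks by class cannot be seen. Splitting the outcome by class is a design choice with its own costs: sparser tables and more comparisons.

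**Conclusion.** The point holds for the answer categories. Use on 1 to 3 days in four weeks has no valid category, in either language version, at the boundary that decides who counts as a user. Under the English averaging wording, 17 to 19 days has none either.

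The consequence is avoidable misclassification in a secondary outcome, which mainly costs sensitivity. Its size cannot be stated: it depends on how many patients use these drugs less than weekly and on how they round, and the protocol gives neither. The power figures above show only a possible range under assumed rates.

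A reader might also infer bias between the arms, because patients know their allocation and choose the rounding themselves. The documents do not show this. Both arms answer the same questionnaire, baseline answers come before randomisation, and knowledge of allocation affects every self-report in an open trial alike. The point is minor, but specific and easily removed.

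**What to change.** Replace the weekly categories with an exhaustive set in days over the recall period, for example 0, 1-3, 4-16 and 17-28 days in the last four weeks, and state that use on one day or more counts as use. These categories cover all 1 + 3 + 13 + 12 = 29 totals and keep close to the present cut-points: 4-16 days equals 1-4 per week, and 17-28 days is 5-7 per week with the uncovered totals 17-19 added. Use the same wording in the English and Danish texts and in the questionnaire.

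The cost is rewording one question, plus one more category and so a somewhat sparser chi2 table. If the data are already collected with the present categories, state how less-than-weekly use was classified, or that no instruction was given, and report this as a limitation of the outcome.

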The baseline measurements are performed by the physiotherapist who sees the patient at he baseline visit 14 days after their discharge. The following tests at 8 weeks and 6 months are performed by a project physiotherapist, who is blinded as to the patient's group allocation. When the patient is summoned for the follow-up tests it is underlined that the patients must not reveal their group allocation.

66      Tabel 1. Overview of measurement timepoints

| Timepoint      | Baseline
14 days after discharge | 1st follow-up
8 weeks after baseline | 2nd follow-up
6 months after baseline |
|----------------|-------------------------------------|-----------------------------------------|------------------------------------------|
| Outcome |                                     |                                         |                                          |
| Incr SWT       | X                                   | X                                       | X                                        |
| PEmb-QoL       | X                                   | X                                       | X                                        |
| EQ-5D          | X                                   | X                                       | X                                        |
| Sick leave     | X                                   | X                                       | X                                        |
| Medication     | X                                   | X                                       | X                                        |

67      *Incr SWT = Incremental Shuttle Walk Test; PEmb-QoL = Pulmonary Embolism Quality of Life*  
68      *Questionnaire; EQ-5D = EuroQol 5 Dimensions*

69

70      **Interventions**

71      *Group 1, usual care:* A usual course of treatment typically entails 3-5 days of hospitalization where  
72      anticoagulant treatment is initiated. The patient and his or her relatives receive general information  
73      about the disease and the course of treatment, the medication, and future prevention of embolism.  
74      Approximately 2 weeks after discharge the patient is seen at the hospital for control of their  
75      medication and the following outpatient visits are planned individually depending on the patient's  
76      needs. Any other treatment that may be offered at the hospitals, e.g. contact with physiotherapists  

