77      during hospitalization can vary between hospitals. The patients are scheduled for physical tests and  
78      completion of questionnaires at 8 weeks and 6 months.

79      *Group 2, homebased exercise:* In addition to usual care, patients are offered participation in an  
80      eight-week home-based exercise program with telephone follow-ups after 1, 2 and 4 weeks.  
81      Following the completion of the baseline measurements the physiotherapist has a dialogue with the  
82      patient regarding the importance of exercise and how the patient can schedule the exercise in their  
83      everyday life. In brief, the patients are recommended to exercise for a minimum of three times per  
84      week for 1 hour, with intervals (20 minutes in total) at a high intensity level, where only very short  
85      sentences of speech are possible). The remaining 40 minutes are at a moderate intensity, where you  
86      are only slightly out of breath, but having a conversation is possible. The patients can choose  
87      whatever type of exercise they prefer, and they are generally encouraged to choose an exercise  
88      modality they already perform, or a modality they have previously had positive experiences with.  
89      The patients record all their training sessions in a diary handed out at the first visit (appendix 5).  
90      The training diary can be handed out in paper or be sent on email. The training diary will be used  
91      for the motivational follow-up calls made by the physiotherapist at 1, 2 and 4 weeks. After the 8  
92      weeks program is finished, the patient brings the diary to the hospital at the subsequent follow-up  
93      test. Patients in the intervention group are scheduled for physical tests and completion of  
94      questionnaires at 8 weeks and 6 months like the control group.

95

96 **Analysis and evaluation:** For the primary outcome, ISWT, parametrical statistics are used to  
97 describe and analyse data, if data are normally distributed. For the secondary outcomes, PEmbQoL  
98 and EQ-5D, data are on an ordinal scale, and hence data are described and analyzed using non-  
99 parametric statistics. Sick leave (number of days) are described and analyzed using parametrical  
100 statistics if data are normally distributed. For the evaluation of psychoactive drugs the chi2 test is  
101 used. The power calculation is based on the ISWT. The smallest clinical relevant difference has  

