### Interventioner:

*Gruppe 1, vanlig behandling:* Et vanligt behandlingsforløb indebærer typisk 3-5 dages indlæggelse hvor antikoagulerende behandling opstartes. Der gives generel information til patient og pårørende om sygdomsforløbet, den medicinske behandling og forebyggelse fremadrettet. Cirka 2 uger efter udskrivelse indkaldes patienten herefter til kontrol af deres antikoagulerende medicin, og efterfølgende kontroller aftales individuelt efter behov. Øvrig behandling der tilbydes, fx kontakt til fysioterapeut under indlæggelse, kan variere mellem hospitalerne. Patienterne indkaldes til fysiske tests og udfyldelse af spørgeskema ved 8 uger og 6 mdr.

*Gruppe 2, hjemmetræning:* Udover vanlig behandling tilbydes patienterne at deltage i et 8 ugers hjemmetræningsforløb med opfølgende telefonkontakt efter 1 uge, 2 uger og 4 uger. Efter gennemførelsen af baseline målingen har fysioterapeuten en samtale med patienten omkring

vigtigheden af træning og hvordan patienten bedst kan tilrettelægge træningen i sin hverdag. Kort fortalt opfordres patienten til at træne minimum 3 gange om ugen af én times varighed, med indlagte intervaller (i alt 20 min) på intensivt niveau, svarende til at man kun tale i korte sætninger. De resterende 40 min er i moderat intensivt, hvor man bliver lettere forpustet, men hvor samtale er mulig. Patienterne må selv vælge træningsformen, og de opfordres til at vælge en træningsform de dyrker i forvejen eller har positive erfaringer med. Patienterne skal registrere alle deres træningspas i en træningsdagbog (Bilag 5). Træningsdagbogen kan patienten enten få udleveret i papirform eller få tilsendt per e-mail. Træningsdagbogen bruges som udgangspunkt for de motiverende opfølgningssamtaler (telefonisk), som fysioterapeuten foretager efter hhv. 1, 2 og 4 ugers træning. Efter de 8 ugers træning er afsluttet medbringer patienten træningsdagbøgerne til deres første opfølgende test på hospitalet. Er dagbøgerne udfyldt elektronisk indsendes de per mail. Patienterne indkaldes til fysiske tests og udfyldelse af spørgeskema ved 8 uger og 6 mdr. ligesom kontrol gruppen.

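### Only the exercise arm keeps a training diary, and it is brought to the 8-week test run by the blinded physiotherapist, with nothing said to keep it from the assessor

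*Protocol*

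**What the plan says.** Four parts of the Protocol bear on this.

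- **Assessor.** In the English Methods, under outcomes and methods of measurement: "The following tests at 8 weeks and 6 months are performed by a project physiotherapist, who is blinded as to the patient's group allocation". The Danish text says the same.
- **Safeguard.** When patients are summoned for follow-up, "it is underlined that the patients must not reveal their group allocation". This is the only measure described for keeping the assessor blinded.
- **Diary.** A training diary is described only for Group 2, home-based exercise. On its form: "The training diary can be handed out in paper or be sent on email". On its return, after the 8 "weeks program is finished, the patient brings the diary to the hospital at the subsequent follow-up" test. The Danish section Interventioner specifies the first follow-up test: "medbringer patienten træningsdagbøgerne til deres første opfølgende test på hospitalet". It adds an exception that the English text lacks, for diaries completed electronically: "Er dagbøgerne udfyldt elektronisk indsendes de per mail".
- **Endpoint.** The primary outcome is "Change in physical capacity, measured with the Incremental Shuttle Walk Test (appendix 3) from baseline to 6 months follow-up", and "The primary endpoint is 6 months after baseline test". The 8-week measurement is called intermediary.

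**The concern.** Patients know their arm, and so does the physiotherapist who advises and telephones the exercise patients. Blinding of the follow-up assessor is the only blinding the Protocol describes, so it carries the whole protection against detection bias on the walk test. The ISWT is a test of maximum walking capacity and depends on effort. If the assessor knows the arm, encouragement or the judgement of when the walk ends could differ between groups, and part of an observed difference could then come from the assessment rather than the training.

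The diary instruction works directly against this protection. The same patients who are told to conceal their group are told to arrive at the blinded visit with an item that only their group possesses. The Protocol fixes this procedure itself; it is not a detail one would expect to find later in a statistical analysis plan.

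**Working it through.** The point is procedural, so the main check is to set the provisions side by side.

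1. **Who has a diary?** Group 2 only. The description of Group 1 (usual care) mentions none. A visible diary is therefore specific to one arm.
2. **When is it brought?** At the follow-up test after the 8-week programme. The Danish text confirms that this is the first follow-up, which Table 1 places 8 weeks after baseline.
3. **Who runs that test?** The blinded project physiotherapist.
4. **Who receives the diary?** Neither version says. The destination is the hospital, at the test visit; no other recipient is named and no separation from the test is described.
5. **Which measurement is directly exposed?** The 8-week ISWT. Baseline precedes randomisation and cannot be affected. No diary is scheduled for the 6-month visit.
6. **Can it reach the primary outcome?** Only if the assessor sees the diary at 8 weeks, the same individual tests that patient about four months later, and that person remembers. The Protocol gives both tests to the same role but does not say that one individual does both. With 140 patients at five hospitals (140/5 = 28 per hospital on average), a repeat meeting is plausible.
7. **How many patients?** At most 70 of 70 in the exercise arm and 0 of 70 controls. Under the Danish text only those with paper diaries count, and their share is not given.

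**Illustration of sensitivity only.** No assessor bias can be derived from the Protocol, so the shifts below are assumptions.

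- Inputs from the analysis section: difference 60 m, 60 per group, power 80%, significance level 5%. Sidedness and SD are not stated; two-sided is assumed and the SD is solved for.
- Implied SD = 60 × √(60/2) / (1.960 + 0.842) = 328.6 / 2.802 = 117.3 m. The plan's 60 per group cannot be reproduced independently, because this SD is obtained from it.
- SE of the group difference = 117.3 × √(2/60) = 21.4 m.
- With no true effect and an average shift of b metres across the exercise arm, the two-sided rejection rate is Φ(b/SE − 1.96) + Φ(−b/SE − 1.96).

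| Assumed shift b | b/SE | Rejection rate |
|---|---|---|
| 0 m | 0 | 5% |
| 10 m | 0.467 | 6.8% + 0.8% = 7.5% |
| 20 m | 0.934 | 15.2% + 0.2% = 15.4% |

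(The first sum is of rounded terms.) Solving for the SD with the t distribution gives 116.3 m and rates of 7.6% and 15.6%. The shift b is an average over the whole arm: if only half the arm were exposed, a 20 m effect in those patients would average 0.5 × 20 = 10 m, and the 10 m row would apply.

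**The case against.** The strongest reply is that nothing here proves unblinding. The diary goes to the hospital, not expressly to the assessor, and both instructions can be obeyed if other staff collect it. The patient information and diary appendices, which are not shown, may say how it is returned. Electronic diaries are mailed under the Danish text. The 8-week test is intermediary and no diary is due at 6 months. The assessor's discretion in the ISWT depends on the test procedure in an appendix that is also not shown, and the bias sizes above come from no document.

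Much of this stands, and it limits what can be claimed. A reader might infer that the diary necessarily reveals allocation and so breaks the blinding of the primary outcome for the whole exercise arm, leaving a positive result uninterpretable. The Protocol does not support that: disclosure is a risk and not a stated event, the directly exposed measurement is the one at 8 weeks, carry-over needs the three conditions in step 6, and the number of paper diaries is unknown.

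The reply does not remove the conflict. The main text ties the diary to the test visit, names no one else to receive it, and relies on patients' silence while asking one arm to carry a visible marker. In the English version even the exception for electronic diaries is absent.

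**Conclusion.** The concern holds as a risk that the Protocol itself creates. The diary instruction conflicts with the instruction that patients conceal their group. It can unblind the intermediary 8-week ISWT for exercise patients with paper diaries, at most 70, and may carry over to the 6-month primary ISWT if the same physiotherapist tests the patient again.

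This rests on two readings: that controls keep no diary, since none is described for them, and that no handover arrangement exists beyond the text shown. The rates of about 8% and 15–16% for shifts of 10 m and 20 m rest on assumed shifts and a back-solved SD. They show how sensitive the comparison would be to assessor bias; they are not an estimate of bias in this trial, and the conclusion does not depend on them. The point is still worth settling before the first 8-week visit, because blinding lost at a test cannot be restored in the analysis.

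**What to change.** Replace the diary-return sentence in both language versions. Diaries should be returned by e-mail or post, or handed to named unblinded staff away from the test, and should never be taken to the test itself. The Danish text already provides the e-mail route, so the English version should be brought into line with it. Add to the follow-up summons, next to the reminder not to disclose the group, that the diary must not be brought to the test.

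The cost is one amended sentence in each version, a line in the summons, return envelopes for paper diaries, and slightly more chasing of unreturned ones. Having the assessor record a guess of the allocation after each test would show whether blinding held; this is optional and not needed to resolve the conflict.
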